#### Analysis plan

The EPDS, GAD7 and IES-R scores between intervention and control groups will be directly compared. We will also compare the proportions of women with EPDS score of >10 and>15 in the two groups.

#### Confounders

Socioeconomic status, educational level, parity, obstetric history including history of complications and trauma during previous pregnancies, number of surviving children, history of chronic diseases and use of medication, complications developing during current pregnancy (such as preeclampsia, gestational diabetes etc) may all be confounders.

#### Patient and public involvement

No patients or public have been involved in the design, recruitment or conduction of the study.

#### Significance

Our study will generate evidence on whether web-based early intervention programmes could be efficient in ameliorating the risk and severity of perinatal mental health disorders and inform best clinical practice for women affected by the consequences of the COVID-19 pandemic.

This multicentre RCT to be conducted in Hong Kong and Shanghai is expected to provide access to an adequate sample size and external validity as well as insight into socioeconomic and cultural specifics of perinatal mental health disorders. Mental health disorders contribute up to 30% of the global burden of disease^53^ and their prevalence is expected by rise during the COVID-19 pandemic. Intergenerational transmission of maternal perinatal mental health disorders has been shown to impact the child’s physical and mental development.^19 54^ These risks might be heightened in the time of the COVID-19 pandemic. Our RCT intends to provide some insight into consequences of the COVID-19 pandemic on pregnant women’s mental health status and pregnancy outcomes.

This interdisciplinary collaboration project may fill the research gap regarding the relationship between mental health and social environments. The study will raise awareness of mental healthcare and highlight the feasibility and value of web-based psychosocial support as a cost-effective way of preventing/ameliorating mental health disorders in mothers and their families during the COVID-19 pandemic.

#### Equipment and infrastructure

Hong Kong’s maternity hospitals and the Shanghai Maternity and Child Healthcare Hospitals have about 11 027 and 117 700 respective deliveries annually. All the places have the necessary infrastructure to facilitate patient recruitment for research, conducting interviews and distributing survey questions.

## Ethics and dissemination

### Adverse events

Peer to peer support is widely used for mental health promotion among adolocent and women. Previous research has demonstrated that peer supportive relationships help contribute to positive adjustment and to buffer against stressors and adversities, including psychiatric problems.^28^

No serious adverse effects are expected to occur as a result of our intervention, that is, web-based psychological support. Any adverse event, defined as a serious undesirable experience/event or injury associated with the use of the study intervention, will be reported to the health authorities of the respective study location and principal investigator. All participants will be covered by the national health insurance plans of the respective study sites.

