## Material and methods

### Trial design and setting

The Mental health of Urban Mothers trial is a prospective randomised controlled trial that will be performed in order to assess the effects of psychosocial support during pregnancy that focuses on factors that can reduce mental health problems and adverse outcomes in pregnant and postpartum women (intervention) versus standard care (control group). The intervention will be delivered by trained peers. Participating women will be recruited from two large urban areas, that is, Hong Kong (7.5 million inhabitants and among all maternity hospitals 11 027 annual deliveries^36^ and Shanghai (25 million inhabitants and Shanghai Maternity and Child Healthcare Hospital with more than117 700 deliveries per year). The intervention group will receive web-based psychosocial peer-to-peer support two times during the antenatal period before 36 gestational weeks (at 18–22 weeks and 24–28 weeks) and the control group will receive the usual standard antenatal care. Mental health status will be assessed using standard questionnaires, that is, EPDS and GAD7 and IES-R. Information on the course and outcome of pregnancy will be obtained by sending a questionnaire at 4–6 weeks postnatally via a web survey.

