### Recruitment and blinding

Pregnant women will be recruited via non-profit organisation websites in each country. In addition to Hong Kong and Shanghai, we aim to include additional urban locations, including Stockholm, Sweden in this multicenter study. Via web link, the women will be guided to the research project website. The peer support website includes information about the project and informed consent. By completing the initial sociodemographic survey, the women can consent to participate in the research study. Then, they will ask to use an app to follow the study and complete the survey questionnaires. The participating women will be automatically randomised to intervention (peer-to-peer web-based psychosocial support) or control group (standard care) by the computer-generated random sequence. Regardless of recruitment to the intervention or control group, the women will continue their regular visits at the maternity clinics as usual.

Both the women and their peers will be forbidden to inform anyone in the study about which study group they belonged to. However, due to the nature of intervention, investigators, as well as the study participants, will not be blinded to the intervention.

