#### Control group

They will receive standard perinatal care provided at maternity clinics.

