### Outcome measures

The primary outcome measure is the woman’s EPDS assessed at 34–36 weeks of gestation and at 4–6 weeks postnatally.

Secondary outcomes are GAD7 scores to assess maternal anxiety levels, IES-R score to assess PTSD and pregnancy complications, including occurrence of mental health disorders, rate of preterm birth, rate of induction of labour, rate of vaginal birth, elective caesarean sections on maternal request as well as other birth outcomes.

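### Adverse events are defined as serious and associated with the intervention, so their counts give no comparison between the randomised arms

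*Protocol article*

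**What the plan says.** The Adverse events section of the protocol article gives one definition. An adverse event is "defined as a serious undesirable experience/event or injury associated with the use of the study intervention", and any such event "will be reported to the health authorities of the respective study location and principal investigator". The same paragraph states the expectation that "No serious adverse effects are expected to occur as a result of our intervention". The article has no wider category of event.

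On the control arm, the Control group section says: "They will receive standard perinatal care provided at maternity clinics". The Recruitment and blinding section says that "investigators, as well as the study participants, will not be blinded to the intervention".

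Other parts of the article plan data that bear on harm:

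- Outcome measures names EPDS as primary. The secondary outcomes are GAD7, IES-R and "pregnancy complications, including occurrence of mental health disorders, rate of preterm birth, rate of induction of labour, rate of vaginal birth", together with further birth outcomes.
- Analysis plan says: "The EPDS, GAD7 and IES-R scores between intervention and control groups will be directly compared".
- Trial design and setting says: "Information on the course and outcome of pregnancy will be obtained by sending a questionnaire at 4–6 weeks postnatally via a web survey".

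**The concern.** An adverse event record serves a randomised comparison only if the same event would be entered in either arm. Here entry depends on a link to the intervention, which is possible in one arm only. It depends also on a judgement of that link, made in a trial where allocation is known and no serious harm is expected.

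Two things are at stake. First, a count of adverse events by arm could not be read as evidence for or against harm. Second, an acute event that the outcome instruments do not record, such as a crisis, self-harm or an emergency admission between assessments, is reportable only if someone attributes it to the support sessions. A background event and an event caused by the intervention are then separated by opinion rather than by randomisation.

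**Working it through.** The plan attaches no figure to adverse events, so there is none to reproduce. The check is to follow the definition through each arm.

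**Inputs**

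- Women per arm, N: the Sample size section asks for 100 women per city in two cities, 200 in all. Equal arms give N = 200 / 2 = 100 (50 per arm in each city).
- True proportions with an undesirable event, p1 (intervention) and p0 (control): not given. Assumed values of 2%, 5% and 10% serve as illustration.
- Fraction of intervention-arm events attributed to the intervention, a: not given; anything from 0 to 1.

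**What the definition counts**

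- Control: no use of the intervention, so the attributable fraction is 0 and the expected count is N × p0 × 0 = 0.
- Intervention: the expected count is N × p1 × a.
- Difference between arms: N × p1 × a − 0 = N × p1 × a.

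The control rate p0 has dropped out. The recorded difference therefore carries no information on p1 − p0, whatever the rates are.

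**Illustration with no true harm (p1 = p0 = p)**

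| Assumed p | True events expected per arm, N = 100 | Countable, control | Countable, intervention (a from 0 to 1) |
|---|---|---|---|
| 2% | 100 × 0.02 = 2 | 0 | 0 to 2 |
| 5% | 100 × 0.05 = 5 | 0 | 0 to 5 |
| 10% | 100 × 0.10 = 10 | 0 | 0 to 10 |

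With 50 per arm in one city, the true expectations are 1, 2.5 and 5, and the control count is again 0.

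**When the outcome instruments look**

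Support is given at 18–22 and 24–28 weeks. The scales are given at 34–36 weeks and at 4–6 weeks after birth. The first scale assessment follows the first contact by 34 − 22 = 12 to 36 − 18 = 18 weeks, and the second contact by 34 − 28 = 6 to 36 − 24 = 12 weeks. A symptom score taken then need not show an acute event that has since passed. A woman who drops out after such an event has her score imputed, and the imputed score does not show the event.

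**The case against.** The strongest objection is that the harms most plausible for peer support are already trial outcomes. Worse depression, anxiety or stress scores, new mental health disorders, preterm birth and other birth outcomes are collected with the same instruments in both arms, and none of them passes through the adverse event definition. This stands. A reader might infer from the definition that harms cannot be compared between arms at all; the article does not support that.

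The second objection is that the sentence is a reporting rule. It says what goes to the authorities and the principal investigator, not that nothing else is recorded, and no between-arm analysis of adverse events is planned. The full protocol may hold recording rules, and an external data monitoring committee is named. This stands in part. The article does not announce a safety conclusion, and none should be attributed to it. But the sentence does more than route reports: it defines the term, with no wider category beside it. That is a stated rule rather than a detail left out of a condensed article.

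Third, the article does not say who judges association, sets out no adjudication step, and leaves open whether the word serious also covers injury. That is fair. The point needs only that the link to the intervention qualifies the whole phrase, and that nobody in a position to judge is described as blinded.

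Finally, with so few expected events, a comparison would tell little even after a change. That is true, and it is why only descriptive tabulation is suggested. The one-sided 95% upper limit for 0 events in 100 women, 1 − 0.05^(1/100) = 2.95%, likewise reflects the sample size and not this definition.

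**Conclusion.** The point holds in a limited form. As defined, adverse events are zero in the control arm by construction and depend on open-label attribution in the intervention arm, so their counts give no randomised comparison. This follows from the wording alone and needs no assumed event rate; the 2% to 10% range only shows the scale, which is a handful of events per arm. Acute events outside the outcome instruments have no arm-neutral route into the adverse event record that the article describes.

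Harms measured as trial outcomes can still be compared between arms, and the primary EPDS inference is unaffected. The change is worth making because it is cheap, not because the trial's main conclusion depends on it.

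**What to change.** - Define an adverse event as any undesirable event or injury in any randomised woman, from randomisation to the last assessment, whatever its relation to the intervention.
- Collect it in the same way in both arms, through the questionnaires already planned at 34–36 weeks and at 4–6 weeks after birth.
- Classify seriousness and relatedness separately, after the event is recorded.
- Keep the existing reporting to the authorities and the principal investigator.
- Tabulate events by randomised arm, descriptively and without a formal test.

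The cost is a revised definition, one extra item in two questionnaires and more events to log. Two limits remain. Women who drop out may still be missed. And since women enter at 12–18 weeks, the first questionnaire asks them to recall 34 − 18 = 16 to 36 − 12 = 24 weeks, with the same limitation in both arms.

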### Dissemination plan

The study team plans to implement a knowledge translation using conventional methods for dissemination of scientific results, as well as modern communication strategies such as social media. The information about the study will be spread through established collaborations with non-profit organisations in Hong Kong and Shanghai, via Chinese American Psychoanalytic Alliance and the Shanghai Centre for Women’s and Children’s Health. We will use patient support groups, scientific and professional (midwifery, obstetric and psychological therapy), to communicate about our study.

We will use established scientific channels to communicate with the wider scientific community by publishing our protocol in an open access journal. We will also communicate our findings by presenting at national and international scientific meetings, along with publishing in a peer-reviewed international scientific journal.

We will also use more modern techniques, such as social media, to disseminate our findings to the public.

## Discussion

This RCT will provide high-quality data about the effect of web-based psychosocial peer-to-peer intervention during pregnancy on maternal mental health. A recent review by Howard *et al*^55^ has shown that psychological and psychosocial interventions could be effective treatments for postnatal depression. Some studies from low-income and middle-income countries have shown that these treatments can be provided effectively by trained peers or non-specialist workers.^56^ Evidence on the treatment of antenatal depression is limited to small trials (with 36–53 women) of interpersonal therapy, culturally relevant brief interpersonal psychotherapy and CBT.^57–59^ Little research exists about the effectiveness of such interventions (including web based) for other perinatal mental health problems.^55^

The information generated by this project could provide the basis for public health policies to be put in place and resource allocation for supporting pregnant and postpartum women suffering from depression, anxiety and PTSD, as a result of the COVID-19 pandemic.

The implementation of a culturally sensitive maternal mental health education addresses the need for more awareness of mental health issues in antenatal care. Our RCT can fill a knowledge gap and provide information on effectiveness of antenatal interventions provided by trained peers. Several studies have shown the effect of antenatal maternal mental health problems on child outcomes postpartum.^60–62^ Social and emotional support reduces associations between postnatal depression and early cognitive development in the child.^63^ The lack of recognition of perinatal mental health, distress and disorders may have serious implications for negative long-term effects on both mother and infant.^62 64^ Therefore, it is important to recognise the transgenerational effect of perinatal mental health disorders and to intervene early to avoid negative outcomes for the child.

The study’s assessment of women’s mental health status at the end of the pregnancy provides information on the expected benefits of psychosocial support during antenatal care, with emphasis on cost-effective web-based psychosocial peer-to-peer support as an important alternative care model. Two recent studies have shown that as many as three out of four pregnant women use a pregnancy-related internet application and find these applications beneficial and trustworthy.^65 66^ This is likely to be even more relevant in urban dwellers.

The routines in perinatal mental health screening policies share similarities, yet they are still different in some aspects in Hong Kong and Shanghai. In Shanghai, first universal prenatal health screening policies have been put in place recently, that is, at Shanghai Jiading District Maternity and Child Health Care Hospital and Obstetrics and Gynecology Hospital of Fudan University.^67 68^ Currently, Shanghai provides only limited universal screening for perinatal mental health problems and lacks universal screening on provincial level. Adequate care for all pregnant women with increased risk for developing perinatal mental health problems is currently not available in Shanghai. In Hong Kong, however, universal PPD screening is one of the components of the Comprehensive Child Development Service in maternal and child health clinics, in collaboration with the Hospital Authority and Social Welfare Department.^69^ Further, Hong Kong women attending perinatal healthcare can get access to a webpage provided by the government, promoting the spread of public health information as well as raised awarness about perinatal depression and services provided for pregnant and postpartum women and their families.^69^ The resource allocation for universal screening and access to information might be crucial in order to reduce the burden of disease caused by perinatal mental health disorders on the family and the society. Our study compares the impact of intervention in two different healthcare settings.

As for most randomised trials, the external validity/generalisability of our findings could be limited since we will only target urban-dwelling population who are comfortable in using internet-based applications.
